### Recruitment & randomization

**Interventions**

Participants randomized to the intervention group receives Obeticholic acid [OCANASH
^®^ (Macleods Pharmaceuticals) or OCABILE
^®^ (Torrent Pharmaceuticals)], while those in the comparator group receives Ursodeoxycholic acid [URSETOR
^®^ (Torrent Pharmaceuticals)].

**Allocation**

Participants are randomized in a 1:1 ratio using a computer-generated permuted block sequence. Allocation concealment will be ensured using sequentially numbered, sealed opaque envelopes opened by the study pharmacist on postoperative day two.

**Blinding**

This is an open-label study. Blinding is not feasible due to the nature of the interventions. Given the difference in tablet size and dosing frequency (three times daily for UDCA vs once daily for OCA), blinding is not being done.

Primary outcomes will be based on objective biochemical parameters to minimize bias.

Given the difference in tablet size and dosing frequency (three times daily for UDCA vs once daily for OCA), blinding is not being done.

Follow-up visits for physical examinations and safety assessments are being scheduled during the study period at the following intervals: one month, three months, six months, and twelve months post-transplant (
Figure 1).

Study assessments were initiated at one month post-transplant because a substantial proportion of our liver transplant recipients are high-MELD patients who often have markedly elevated bilirubin and cholestatic enzyme levels in the immediate postoperative period. In addition, transient elevations in liver function tests are commonly observed during the early post-transplant phase due to ischemia–reperfusion injury, surgical factors, sepsis, or early graft dysfunction or rejection.

In live donor liver transplantation, particularly among high-MELD recipients, these fluctuations are often pronounced during the first few weeks after surgery. Therefore, a four-week stabilization period was allowed to enable resolution of early postoperative variability and to ensure that subsequent biochemical measurements more accurately reflect the effects of the study intervention rather than perioperative factors.

Liver function tests, C-reactive protein (CRP), platelet count, prothrombin time/international normalized ratio (PT/INR), fasting blood sugar (FBS), tacrolimus concentration, and other relevant parameters are being measured at each follow-up visit. Lipid profile—including total cholesterol, low-density lipoprotein (LDL), high-density lipoprotein (HDL), very low-density lipoprotein (VLDL), and triglycerides (TG)—as well as glycosylated hemoglobin (HbA1c) levels, are being assessed at pre-transplant admission, and at three, six, and twelve months post-transplant.

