## Methods

### Trial design

This is a single-center, open-label, parallel-group randomized controlled trial conducted at a tertiary care liver transplant center.

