### Biopsy and rejection evaluation

A biopsy is being performed when suspected rejection (unexplained rise in transaminases) is observed. The biopsy results are being evaluated based on the Rejection Activity Index score and the Banff criteria. Data on the frequency and duration of the first biopsy-proven acute rejection (BPAR) episode (within six months of transplantation) that requires therapy are being recorded. Any biliary system-related strictures, leaks, or anastomosis issues are being documented. Early allograft dysfunction (EAD) is being assessed using the criteria developed by Olthoff et al.
^
7,
32
^

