### Adverse reactions and causality assessment

Adverse events are being captured by direct interview of patients during the routine follow-up visits. We are capturing the pruritus by physical examination, vital signs and 5D pruritus questionnaire and documented systematically using structured Case Report Forms (CRFs) to ensure standardized data collection and analysis. The Naranjo algorithm will be used to establish causality and then classify them as definite, probable, possible, or unlikely.

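### Blinding is ruled out for a reason that concerns only taking and giving the drug, so nothing keeps the arm from those who grade biopsies or attribute deaths to rejection

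*Protocol article*

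**What the plan says.** Under Trial design: "This is a single-center, open-label, parallel-group randomized controlled trial conducted at a tertiary care liver transplant center".

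The Blinding section opens with the general statement that "Blinding is not feasible due to the nature of the interventions" and then gives the specific grounds: "Given the difference in tablet size and dosing frequency (three times daily for UDCA vs once daily for OCA), blinding is not being done". That sentence appears twice, and no exception is made for anyone who assesses outcomes. The protection offered is one line: "Primary outcomes will be based on objective biochemical parameters to minimize bias".

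Biopsy and rejection evaluation describes how rejection is found and graded. First, "A biopsy is being performed when suspected rejection (unexplained rise in transaminases) is observed"; then "The biopsy results are being evaluated based on the Rejection Activity Index score and the Banff criteria". For biliary events: "Any biliary system-related strictures, leaks, or anastomosis issues are being documented". The Secondary outcomes list includes biopsy-proven rejection, biliary complications, all-cause mortality and, separately, death due to rejection. None of these sections says that the reader or classifier is unaware of the arm.

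**The concern.** The decision is wider than the reason given for it. Different tablets and different dosing frequencies cannot be hidden from patients or from the staff who give the drugs. A pathologist grading a slide, or a person deciding whether a death was due to rejection, handles no tablets.

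The protocol recognises that open-label treatment can bias outcomes, since it offers a safeguard, but that safeguard is stated for the primary outcomes only. The judged secondary outcomes are left without one. Under Expected results the protocol anticipates fewer biliary complications and fewer deaths on OCA, so there is a stated direction in which borderline calls could drift. The primary endpoint is described in the article as a surrogate marker of response, so any claim of clinical benefit would have to draw on outcomes of this judged kind.

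**Working it through.** There is no figure in the plan to reproduce. The check is to take each outcome, ask whether a judgement is involved, and see whether the stated reason or the stated safeguard reaches it.

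| Outcome | Judgement involved | Covered by the stated safeguard? | Does the tablet or dosing reason prevent masking? |
|---|---|---|---|
| ALP and GGT (primary) | Little: laboratory values | Yes | Not relevant |
| ELISA markers | Little: quantitative assay in a centralized laboratory | No, but little exposed | No |
| All-cause mortality | Little: a count | No, but little exposed | No |
| Biopsy-proven rejection | Deciding to biopsy, then grading by Rejection Activity Index and Banff | No | Not for the slide reader |
| Biliary complications | Classifying strictures, leaks and anastomotic problems | No | Not for a classifier working from records |
| Death due to rejection | Attributing the cause | No | Not for a classifier working from records |
| Adverse event causality | Naranjo scoring | No | Scoring needs the suspect drug to be known |

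The table leads to three observations.

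1. The gap is real for rejection grading, biliary events and cause-specific death. Each needs a judgement, none is covered by the safeguard, and the stated reason does not prevent masking.
2. Masking the slide reader protects the grade only. Two open decisions remain in biopsy-proven rejection: whether a transaminase rise counts as unexplained and leads to a biopsy, and whether the episode is one that requires therapy.
3. Causality scoring does not belong with the others, because causality to a drug cannot be scored from a record with the drug removed.

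**Scale.** The article gives no rejection rate and no figure for grading disagreement, so the bias cannot be estimated. The sensitivity to a single call can be shown from the planned 110 to 120 patients per arm (Sample size):

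- 1/110 = 0.9 percentage points
- 1/120 = 0.8 percentage points

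Each biopsy moved across the rejection threshold in one arm therefore shifts that arm's rate by 0.8 to 0.9 percentage points. How many would move is unknown, so this is a unit of sensitivity and not an estimate of bias.

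**The case against.** The strongest reply is that the finding makes too much of silence. In the Blinding section the tablet reason and its conclusion form one sentence, whose natural subject is masking of treatment. What a pathology request form shows is an operational detail that a condensed article may leave to the full protocol. This stands in part: a reader might infer that assessors are known to be unmasked, and the text does not say so. It does not remove the point, because the section also declares blinding infeasible in general terms, makes no exception for assessors, and limits its own safeguard to the primary outcomes. That is a stated decision whose reason falls short of its scope.

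Other objections also carry weight:

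- **Named criteria narrow discretion.** Banff and the Rejection Activity Index for biopsies, and structured case report forms for adverse events, count for something. They are not masking, and borderline calls remain.
- **Coded data.** The Confidentiality section says that data are anonymized and coded. This concerns privacy during analysis and reporting, and does not say that the arm is withheld from an assessor.
- **Adverse events and deaths.** The Secondary outcomes list has any adverse events, with no causality filter, and all-cause mortality. Neither safety nor mortality therefore rests solely on an attributed cause. This stands.
- **Causality and ELISA.** A reader might extend the point to masking causality scoring and assays. The documents do not support this: "The Naranjo algorithm will be used to establish causality and then classify them as definite, probable, possible, or unlikely" describes a task that needs the drug to be known, and the ELISA results are quantitative.
- **Cost.** Classifying biliary events and deaths from redacted records may need an additional person unaware of the arm, at a single center where the investigator transcribes the data. This stands, and the fix is limited accordingly.

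**Conclusion.** The concern holds in a limited form. The protocol rules out all blinding on grounds that apply to those who take or give the drug, and its only stated safeguard stops at the primary outcomes. Nothing in the text keeps the arm from those who grade biopsies or attribute deaths to rejection; biliary events are exposed in the same way.

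The impact is on secondary outcomes. A reader might infer that the primary comparison is compromised as well. The documents do not support that, because ALP and GGT are laboratory values, and all-cause mortality is likewise little affected. The amount of bias is unknown; it depends on the number of borderline biopsies and on what assessors actually know, and the article states neither. The change is worth making because it is cheap and recruitment is still open (Study status), not because a bias of known size has been shown.

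**What to change.** Keep treatment open-label and amend the Blinding section as follows:

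- State who is aware of the arm.
- State that the existing pathologist grades biopsies by Rejection Activity Index and Banff with the arm withheld from the request form. This needs no extra reader.
- Where existing staff unaware of the arm are available, state that they classify biliary events and cause of death without reference to it. Where they are not, say so.
- Report biopsies already read with the arm known as such, separately from those read with it withheld.

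Causality scoring should stay as it is. Putting only study codes on ELISA samples is optional and gains little.

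The cost is minor administrative work. Masking will be imperfect where clinical notes mention the drug. Enrolment has run since December 2021, so the trial will hold a mix of unmasked and masked reads. The decisions to biopsy and to treat rejection remain with staff who know the arm, so some ascertainment bias in biopsy-proven rejection will remain and should be acknowledged when the results are reported.

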**Figure 1. f1:**
[figure not shown]
Flow chart showing study methodology.

We selected a 15% reduction in both alkaline phosphatase (ALP) and gamma-glutamyl transferase (GGT) as our primary biochemical endpoint based on evidence from previous trials in cholestatic liver disease. Specifically, the landmark study by Nevens et al., published in The New England Journal of Medicine (2016), evaluated obeticholic acid in patients with primary biliary cholangitis and used a composite endpoint that included a ≥15% reduction in ALP as part of the therapeutic response criteria.

Although this trial was not conducted in post–liver transplant patients, it provided a strong precedent for using ALP-based endpoints to assess treatment response in cholestatic conditions. We extended this rationale by including GGT alongside ALP, as the combination of these two enzymes provides a more comprehensive and sensitive assessment of cholestasis, particularly in the post-transplant setting where bile duct injury and graft function are dynamic.

Given the lack of clinical trials of OCA in the liver transplant population, this combined biochemical endpoint serves as a reasonable and evidence-informed surrogate marker of response in our study.

Secondary endpoint serum markers are being assessed using an enzyme-linked immunosorbent assay (ELISA) [ELK Biotechnology™] at the centralized biochemistry laboratory. Blood samples collected during the one-month and twelfth-month post-transplant follow-up visits are being used for ELISA testing.

In addition, demographics, patient characteristics, and other critical study details (e.g., medication history, medical history, social habits, family history, and use of other medical systems) are being collected through direct patient or bystander interviews, doctor consultation notes, hospital health information systems, and case records. The collected data is being transcribed into a pre-designed proforma (data collection form) by the investigator.

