### Sample size

The sample size was calculated based on a pilot study comparing the effect of obeticholic acid (OCA) and ursodeoxycholic acid (UDCA) on cholestatic injury in post-liver transplant patients. In the pilot study, the difference in alkaline phosphatase (5.131 ± 39.639 vs 12.496 ± 52.139) was observed between the two groups. With 80% power and 95% confidence, the minimum sample size required was determined to be 108 patients in each group, totaling 216 samples. We will be recruiting around 110 to 120 patients per arm. The calculation was based on the expected difference in ALP reduction between groups observed in pilot data.

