### Statistical analysis

•To compare the means of continuous variables between groups (Drug A vs Drug B), an independent sample t-test will be used at each time point.•To compare the changes in continuous variables from pre- (1 month) to post-transplant (3, 6, and 12 months), a paired t-test will be applied.•To compare the means of variables from baseline to subsequent time points within each group, repeated measures ANOVA will be used if significant. Repeated measures analysis will be used to assess longitudinal changes over time, and Bonferroni correction will be applied for multiple comparisons where appropriate.

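### The one between-arm test named for continuous ALP and GGT is an unadjusted t-test; pre-specifying adjustment for pre-transplant MELD would be a cheap gain in precision, of unknown size

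*Protocol article*

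**What the plan says.** All references are to the protocol article.

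- **Blinding section, on timing of assessments.** The authors explain why assessments start at month 1: "a substantial proportion of our liver transplant recipients are high-MELD patients who often have markedly elevated bilirubin and cholestatic enzyme levels". This is tied to the period immediately after surgery. They add that in living-donor transplantation, "particularly among high-MELD recipients, these fluctuations are often pronounced during the first few weeks after surgery". Their answer is to wait four weeks, so that later measurements reflect the drug more than the operation.
- **Allocation.** "Participants are randomized in a 1:1 ratio using a computer-generated permuted block sequence". Envelopes are opened on postoperative day two. No stratification factor is named.
- **Statistical analysis.** For means of continuous variables between groups, "an independent sample t-test will be used at each time point". Paired t-tests and a repeated-measures analysis are also listed. No covariate is mentioned.
- **Primary outcomes.** The primary endpoint is a proportion: patients whose ALP and GGT fall by at least 15% from month 1. The analysis section names no test for proportions.
- **Data collection, under Figure 1.** The investigator records "demographics, patient characteristics, and other critical study details" from interviews, hospital systems and case records. MELD is not in the list of examples.

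**The concern.** The article singles out a pre-transplant severity score as related to the enzymes under study, and then uses it neither in the randomisation nor in the named between-arm test. Two things could follow if MELD still predicts ALP or GGT at months 3, 6 and 12. First, the variation that MELD explains stays in the error term, and the confidence interval for the difference between arms is wider than it need be. Second, if the arms happen to differ in MELD, the estimated difference moves for a reason unrelated to the drug, and the t-test has no term to correct it.

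The responder endpoint could be touched by another route. Its reference value is month 1. If some MELD-related elevation is still present then, a patient with a raised starting value has more room to fall.

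MELD is also a safer covariate here than the month-1 enzyme value. The month-1 value is measured after allocation, so treatment may already have altered it. Pre-transplant MELD is fixed before allocation.

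**Working it through.** **Inputs from the Sample size section.** "With 80% power and 95% confidence, the minimum sample size required was determined to be 108 patients in each group, totaling 216 samples"; "the difference in alkaline phosphatase (5.131 ± 39.639 vs 12.496 ± 52.139) was observed between the two groups"; "We will be recruiting around 110 to 120 patients per arm". I read 95% confidence as a two-sided 5% level.

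**Step 1: the stated 108 per arm.** With equal arms, n = 2(1.960 + 0.842)² × SD² / difference².
- SD² = (39.639² + 52.139²)/2 = 2144.9, so SD = 46.31.
- Means as printed: difference 12.496 − 5.131 = 7.365, n = 621 per arm. This does not reproduce 108.
- Means with opposite signs: difference 12.496 + 5.131 = 17.627, n = 108.4, or 109 rounded up. A lost minus sign is the likely explanation.

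This is a separate matter. Below, 80% power at 108 per arm is taken as a working premise.

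**Step 2: precision gained by adjusting for MELD.** Let r be the within-arm correlation of pre-transplant MELD with the enzyme value analysed. The article does not give it; I assume 0.1 to 0.5. The residual variance is multiplied by 1 − r². Power becomes Φ(2.802/√(1 − r²) − 1.960), where 2.802 = 1.960 + 0.842. The adjusted analysis needs 108(1 − r²) per arm to match the unadjusted one. The gain in equivalent patients is 1/(1 − r²) − 1.

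| r (assumed) | 1 − r² | Power, from 80% | Per arm to match 108 unadjusted | Equivalent extra patients |
|---|---|---|---|---|
| 0.1 | 0.99 | 80.4% | 107 | 1.0% |
| 0.2 | 0.96 | 81.6% | 104 | 4.2% |
| 0.3 | 0.91 | 83.6% | 99 | 9.9% |
| 0.4 | 0.84 | 86.4% | 91 | 19.0% |
| 0.5 | 0.75 | 89.9% | 81 | 33.3% |

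If the pilot means are right as printed, power at 108 per arm is 21.4% unadjusted, 23.1% at r = 0.3 and 27.1% at r = 0.5. MELD adjustment would not rescue that case: it would need 1 − 108/621, an R² of about 0.83.

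**Step 3: responder proportion.** Assume two equal MELD groups and compare the within-group with the overall binomial variance.
- Response 35% and 55%: 0.2375/0.2475 = 0.960, equivalent to 4.2% more patients.
- Response 30% and 60%: 0.225/0.2475 = 0.909, equivalent to 10.0% more.

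These response rates are assumed.

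**Step 4: chance imbalance.** The standard error of the standardised MELD difference at 108 per arm is √(2/108) = 0.136, so the 95% limit is 1.96 × 0.136 = 0.27 SD. At that limit the ALP difference shifts by 0.267 × r × 46.31:
- r = 0.1: 1.2 units, 17% of 7.365 or 7% of 17.627
- r = 0.3: 3.7 units, 50% or 21%
- r = 0.5: 6.2 units, 84% or 35%

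An imbalance this large or larger arises in about 5% of trials. One above 0.2 SD arises in about 14%, with a proportionately smaller shift at that threshold.

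**The case against.** The case against is strong on four points.

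1. **MELD and the later course.** A reader might infer that the article names MELD as a driver of the enzyme course over the year. It does not. It links MELD to the first weeks, and the four-week wait is its answer. An effect at months 3 to 12, or through the month-1 reference value, is an inference. This stands. The article says only that later values reflect treatment more accurately, so some residual effect is possible, but nothing there shows one.

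2. **Scope of the t-test.** A reader might infer that every between-arm comparison, including the primary one, is a plain t-test. The documents do not support that. The primary endpoint is a proportion with no named test, and it is unclear whether the repeated-measures analysis compares arms. The point is confined to continuous ALP and GGT.

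3. **False positives.** A reader might infer that ignoring MELD inflates the type I error. It does not: over all randomisations it stays at 5%. Conditional on a 0.27 SD imbalance it is about 8% at r = 0.3 and 13% at r = 0.5, but that imbalance is the 95% limit. At 0.2 SD and r = 0.3 it is about 6.2%.

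4. **Covariates as SAP detail.** Choice of covariates often belongs in the analysis plan, and the unadjusted test is legitimate. This stands in part. The article does more than stay silent, since it fixes a specific test that has no place for a covariate.

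It is also fair to say that the article lists other causes of early enzyme elevation, such as ischaemia–reperfusion injury and sepsis, and does not show MELD to be the best predictor. MELD has the practical advantage of being settled before allocation.

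**Conclusion.** This is a cheap improvement and not an error in the plan. As written, neither the randomisation nor the named between-arm test for continuous ALP and GGT uses MELD, although the article itself connects MELD with cholestatic enzymes early after surgery. Adjustment would be sound, because pre-transplant MELD precedes allocation and so cannot absorb a drug effect.

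The size of the benefit cannot be taken from the article. It is negligible at a correlation of 0.2 or less, which is plausible if the early variation settles as the authors expect. It becomes material only at about 0.4 to 0.5, for which the article offers no support. The power figures also assume that the unadjusted comparison has 80% power to begin with. The missing test for the binary primary endpoint and the sample-size inputs that do not yield 108 as printed are larger problems, and this change solves neither.

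**What to change.** In the Statistical analysis section, while recruitment continues and before any summary by arm is seen:

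- For continuous ALP and GGT, replace the independent-sample t-test at each visit with a linear model containing treatment arm and continuous pre-transplant MELD.
- When a test for the responder proportion is set, use a MELD-adjusted, standardised risk difference (for example, from a logistic model), so that the effect measure stays comparable with the unadjusted one.
- Keep the unadjusted comparisons as sensitivity analyses.
- Add pre-transplant MELD to the listed data items.

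The cost is about one sentence in the analysis section, one extra model term and retrieval of MELD from existing records. No new patients, visits or tests are needed. If the correlation proves small, little is gained and almost nothing is lost.
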